This will focus on complementary feeding practices with regard to WHO recommendations, including timing of introduction of solid, semi-solid or soft foods; minimum dietary diversity; minimum meal frequency; minimum acceptable diet and consumption of iron-rich or iron-fortified foods [http://www.who.int/nutrition/publications/infantfeeding/9789241599290/en/] [9]. Data will be collected longitudinally every two months following birth through an interviewer-administered questionnaire to the mother to determine if the child has started feeding on foods/fluids other than breast milk and when they started, frequency of feeding, type of foods/fluids including dietary diversity through 24-hour recall, hygiene practices, and responsive feeding behaviours.

4. Nutritional status as determined by stunting, underweight, and wasting.

Interventions aimed at promoting optimal breastfeeding and complementary feeding practices have been found to reduce malnutrition among infants and young children [35]. It is therefore expected that the proposed intervention will have an effect on the levels of stunting, underweight and wasting. Anthropometric measurements: weight, length/height and mid-upper arm circumference will be collected on the child every two months during the follow-up period. All anthropometric measurements will be carried out according to standard procedures [36]. For determination of underweight, stunting, and wasting, weight-for-age z-scores (WAZ), height-for-age z-scores (HAZ) and weight-for-height z-scores (WHZ), respectively, will be generated using the World Health Organization (WHO) 2006 growth standards [37]. Stunting will be determined as HAZ < -2, underweight as WAZ < -2 and wasting as WHZ < -2 [38].

5. Morbidity from diarrhea.

Evidence indicates that breastfeeding is preventive against infections such as rotaviral diarrhoea [39]. It is therefore expected that promotion of exclusive breastfeeding would impact the rate of diarrhoea morbidity. Data on diarrhea morbidity in the last two weeks for the child will be collected longitudinally through an interviewer administered questionnaire to the mother every two months during the follow-up period.

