### Statistical analysis

Determination of change for the primary outcome (exclusive breastfeeding) will be done at month six. Difference in duration of exclusive breastfeeding will also be determined longitudinally up to six months between the intervention and control groups. Comparison for other outcomes such as morbidity from diarrhea and malnutrition will be done longitudinally at around month three, six, nine and twelve. Analyses will involve a comparison of differences in the intervention and control groups with regard to the primary outcome (exclusive breastfeeding) and secondary outcomes (other infant feeding practices, diarrhea morbidity and nutritional outcomes), controlling for baseline measures (for example, previous breastfeeding practices) and prognostic factors (for example, Socio-economic status (SES) and household food security) if randomization of the clusters does not control for differences in these factors at baseline. Statistical methods to determine change will include analysis of covariance (ANCOVA) for continuous variables (for example, duration of exclusive breastfeeding and any breastfeeding and multinomial logistic regression analysis for categorical variables (that is, whether exclusively breastfed for six months or not) [40]. Additionally, survival analysis (proportional hazard analysis) for variables measured longitudinally (for example, duration of breastfeeding and malnutrition and multilevel modelling for repeated measures such as diarrheal morbidity will be applied. Intention-to-treat analysis [41] will be applied as appropriate. Efforts will be made to maximize follow-up of participants, using the NUHDSS framework to minimize missing information. Quantitative data analysis will mostly be done using Stata version 12.1. (StataCorp LP, College Station, Texas, USA). (See Table 2 for detailed outline of data analysis plan).

**Table 2 T2:** Data analysis outline

**Study objective**	**Outcome variables**	**Independent variable**	**Control variables**	**Type of analysis**
1. To determine the effect of the intervention on breastfeeding and complementary feeding knowledge, attitudes and practices among mothers of infants	1. Knowledge and attitude levels on breastfeeding and other infant feeding practices	Intervention status	SES^1^, food security, maternal demographic characteristics, antenatal care child morbidity	Multinomial logistic regression for rates and survival analysis for duration

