	2. Breastfeeding practices, including initiation of breastfeeding within one hour of birth, exclusive breastfeeding (for first 6 months) and duration of exclusive and any breastfeeding			
	3. Complementary feeding practices for example, optimal timing of initiation of complementary feeding and minimum dietary diversity, minimum meal frequency, and minimum acceptable diet			
2. To determine the effect of the intervention on nutritional outcomes among infants;	1. Stunting	Intervention status	SES, food security, maternal demographic characteristics, child morbidity, antenatal care, vaccination status	Multinomial logistic regression
	2. Underweight			
	3. Wasting			
3. To determine the effect of the intervention on morbidity from diarrhoea among infants	Diarrhoea morbidity	Intervention status	SES, food security, maternal demographic characteristics, child morbidity, antenatal care, vaccination status	Multilevel modeling
4. To determine the experiences, facilitating and limiting factors associated with the intervention	1. Client satisfaction	Not applicable	Not applicable	Descriptive (Outcome 1) Qualitative-thematic analysis (outcomes 2 and 3)
	2. Experiences			
	3. Limiting and enabling factors			
5. To assess the cost-effectiveness of the intervention	Cost-effectiveness	Not applicable	Not applicable	Cost-Effective Analysis

^1^SES=Socio-economic status.

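### Malnutrition is assigned proportional hazards in the text but only multinomial logistic regression in Table 2; no main analysis is named, and the Table 2 model as named covers neither clusters nor repeated visits

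*Protocol article*

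**What the plan says.** All of this is in the protocol article.

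- **Outcome definition** (Outcome measures, secondary outcome 4): "Stunting will be determined as HAZ < -2, underweight as WAZ < -2 and wasting as WHZ < -2". The child's measurements "will be collected on the child every two months during the follow-up period".
- **Statistical analysis, text:** after assigning ANCOVA to continuous variables and multinomial logistic regression to categorical ones, the section adds "survival analysis (proportional hazard analysis) for variables measured longitudinally (for example, duration of breastfeeding and malnutrition" and then "multilevel modelling for repeated measures such as diarrheal morbidity will be applied". It also says that malnutrition will be compared at about months 3, 6, 9 and 12.
- **Statistical analysis, Table 2:** the text refers to the table with the words "See Table 2 for detailed outline of data analysis plan". Its type-of-analysis entries are:
  - objective 1 (feeding knowledge and practices): "Multinomial logistic regression for rates and survival analysis for duration";
  - objective 2 (stunting, underweight, wasting): "Multinomial logistic regression";
  - objective 3 (diarrhoea): "Multilevel modeling".
- **Design:** 14 community units are randomised. The sample size section uses a design effect of 3.2, from an ICC of 0.05 for breastfeeding practices. No ICC is given for malnutrition.

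**The concern.** The two candidate analyses answer different questions. A hazards model concerns the time to a first reading below -2. A logistic model concerns the probability of being below -2 at a given visit. A child can pass the cut-off and recover, and some children may be below it at the first measurement, so the two need not agree. With no main analysis named, the choice could be made after both results are known. The choice also reaches the economic evaluation, which counts malnutrition cases averted: children who were ever below the cut-off and children below it at a set month are different counts.

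The second issue is the model that Table 2 does name. Followed as written, the objective 2 row has no term for the randomised unit and none for several visits by the same child. The row beneath it uses a multilevel method for data of the same shape. An analyst who followed the table literally would obtain standard errors that are too small for the nutrition outcomes.

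**Working it through.** **1. The text set beside Table 2**

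| Outcome | Text | Table 2 |
|---|---|---|
| Breastfeeding duration | ANCOVA; hazards | survival analysis |
| Stunting, underweight, wasting | logistic by the general rule for categorical variables; hazards for malnutrition by name | multinomial logistic only |
| Diarrhoea | multilevel | multilevel |

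Table 2 lists survival analysis for objective 1 and omits it for objective 2. The mismatch is therefore specific to malnutrition and is not a general shortening of the table.

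**2. What the Table 2 model amounts to**

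A multinomial logit with K outcome levels fits K - 1 equations. Each nutrition outcome has K = 2, so one equation remains: binary logistic regression. The label adds nothing, and it carries no random effect or cluster term.

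**3. The protocol's own design effect**

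- Inputs, all from Sample size considerations: 196 women in total before adjustment, design effect 3.2, ICC 0.05, attrition 20%.
- 196 × 3.2 = 627.2, and 627.2 / 0.80 = 784, against the stated figure of about 780.
- 627.2 / 14 = 44.8, or about 45 children per cluster, and 1 + (45 - 1) × 0.05 = 3.2. The stated design effect is reproduced.

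**4. Type I error if clustering were ignored**

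If the true variance is DE times the one used, a nominal two-sided 5% test rejects with probability 2 × [1 - Φ(1.96 / √DE)].

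| ICC | DE, 45 per cluster | 1.96 / √DE | Type I error |
|---|---|---|---|
| 0.05 (protocol, breastfeeding) | 3.20 | 1.10 | about 27% |
| 0.02 (assumed) | 1 + 44 × 0.02 = 1.88 | 1.43 | about 15% |
| 0.01 (assumed) | 1 + 44 × 0.01 = 1.44 | 1.63 | about 10% |

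**5. Repeated visits alone**

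Suppose that four visits per child were pooled as independent and there were no clustering at all. Then DE = 1 + 3ρ, where ρ is the within-child correlation.

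- Assumed ρ = 0.3: DE = 1.9, type I error about 16%.
- Assumed ρ = 0.7: DE = 3.1, type I error about 27%.

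This part does not arise if each time point is analysed separately.

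**The case against.** The strongest reply is that there is little conflict. The three outcomes are categorical, so Table 2 follows the text's general rule. The hazards sentence is introduced as an addition to the methods before it, so it can be read as supplementary. The listed months suit prevalence comparisons by logistic regression. The article nowhere says that clustering will be ignored: the sample size allows for it, and the multilevel sentence gives diarrhoea only as an example. An article also commonly leaves variance estimation to a full analysis plan.

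Much of this stands, and it rules out three stronger readings that a reader might infer.

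- **That neither model can suit these data.** Logistic regression of status at a fixed month copes with a reversible state and needs only a cluster adjustment. Time to first episode can also be defended once the event, the two-month interval in which onset is known, and the clustering are dealt with.
- **That the plan will produce standard errors that are too small.** This follows only if the models are fitted exactly as named.
- **That the hazards analysis would dilute a treatment effect.** The protocol gives no z-score distribution, no correlation between visits and no expected effect on malnutrition, so neither the direction nor the size of such a bias can be derived.

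The reply does not remove the main point. The table presented as the detailed outline drops a method that the text assigns to malnutrition by name, and no order between the two is given. The table also reserves the multilevel method for diarrhoea while naming a different one for nutrition. These are differences between stated entries, not missing detail.

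**Conclusion.** The point holds as an inconsistency to reconcile, together with a badly chosen table entry. The inconsistency rests on the text alone and needs no assumption.

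The size of the second part is conditional on the objective 2 model being fitted as named, without a cluster term. The type I error of a nominal 5% test would then be about 27% if malnutrition clustered as strongly as the protocol assumes for breastfeeding, and about 10% to 15% at assumed ICCs of 0.01 to 0.02 with about 45 children per cluster. The malnutrition ICC is not in the document, so no single figure can be given.

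Only secondary outcomes and the economic evaluation that uses them are affected. The change should be made, but the primary comparison does not depend on it.

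**What to change.** 1. **Table 2, objective 2.** Replace "Multinomial logistic regression" with a multilevel logistic model: visits within child within community unit, with arm, visit and arm-by-visit terms, and a small-sample correction for 14 clusters. A cluster-adjusted logistic analysis at each of the stated time points would serve equally well; if that is chosen, say which two-monthly visit stands for months 3 and 9.
2. **Name that model as the main malnutrition analysis**, in both the table and the text.
3. **Statistical analysis text.** Either remove malnutrition from the hazards sentence or label that analysis supplementary. If it is kept, define the event and state how children already below -2 at the first measurement are handled.

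The cost is a change of wording and a little more analysis work, with no new data. Confidence intervals for the nutrition outcomes will be slightly wider than under a naive fit, which is the honest width.

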### Sample size considerations

The sample size determination was done considering the study design of cluster randomisation since villages in the study sites will be randomised to either control or intervention [29]. A minimum sample size for both intervention and control arms of 196 was estimated to have enough power to detect an increase in exclusive breastfeeding for six months from two per cent (the baseline rate of exclusive breastfeeding in the study setting) [22] to 12%; a ten percentage point increase, although higher increase has been documented in similar interventions elsewhere in the developing world [30]. We used a level of precision of five per cent (for a two-sided *t*-test) and power of 80%. We then adjusted for expected intra-cluster correlation (ICC) using a design effect of 3.2. The design effect was based on an ICC of 0.05, based on previous research on breastfeeding practices in the study area which acts as a baseline for the current study. We allowed for 20% potential attrition, also based on previous research in the study area [31]. Therefore, an effective sample size of about 780 mother-child pairs was estimated. We used practice of exclusive breastfeeding to undertake the sample size calculations as it is our primary outcome of interest. (More detailed account of sample size determination is attached as an additional material in Additional file 1).

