### Assessment

#### *Outcome measures*

##### 

**Primary outcomes** The primary outcome measure is exclusive breastfeeding for six months.

This will involve determining the change in the rate of exclusive breastfeeding for the first six months. Mothers will be advised on what they need to do with regard to breastfeeding and how they should do it, including breast positioning and attachment and expressing and storing breast milk. This advice is expected to lead to self-efficacy with regard to breastfeeding, hence adherence to WHO guidelines on breastfeeding, resulting in improved rates of exclusive breastfeeding for six months. Data on breastfeeding practices will be collected longitudinally from birth every two months through an interviewer-administered questionnaire to the mother. Self-reported exclusive breastfeeding will be validated on a 10% sample using the stable isotope technique (dose-to-the mother of deuterium oxide) for breast milk analysis. The 10% sample will be randomly selected from the list of participating breastfeeding mothers. The procedure will be carried out once per mother-child pair, sampled before the child is aged six months.

##### 

**Secondary outcomes** Secondary outcomes include:

1. Breastfeeding and complementary feeding knowledge and attitudes according to WHO recommendations [9]. Data will be collected every two months following recruitment through an interviewer-administered questionnaire to the mother to determine change in knowledge, attitudes and practice with the intervention.

2. The duration of any breastfeeding in months.

This will include duration of any breastfeeding in months. Data will be collected longitudinally every two months following birth through an interviewer-administered questionnaire to the mother to determine if the child is still breastfeeding, and if so, whether they have started feeding on other foods/fluids other than breast milk; when they started on other foods/fluids; and if they stopped breastfeeding, when they stopped.

3. Complementary feeding practices.

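### Table 2 gives maternal knowledge and attitude levels no method that fits an ordered outcome: only multinomial logistic regression and survival analysis are listed for objective 1

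*Protocol article*

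**What the plan says.** Table 2, which the Statistical analysis section presents as the detailed outline of the analysis, lists three outcomes under objective 1. The first is "Knowledge and attitude levels on breastfeeding and other infant feeding practices". The others are breastfeeding practices (with durations) and complementary feeding practices. One analysis entry serves all three: "Multinomial logistic regression for rates and survival analysis for duration".

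The Outcome measures section lists the same item as secondary outcome 1, "Breastfeeding and complementary feeding knowledge and attitudes according to WHO recommendations". It is collected by questionnaire every two months "to determine change in knowledge, attitudes and practice with the intervention". Knowledge and attitudes are also measured at recruitment (Other data to be collected, item 1.a).

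The Statistical analysis text names "analysis of covariance (ANCOVA) for continuous variables", and its only examples there are how long breastfeeding lasts. For outcomes in categories it specifies "multinomial logistic regression analysis for categorical variables (that is, whether exclusively breastfed for six months or not". ANCOVA appears in no row of Table 2, and no ordinal model is named anywhere. The number of levels, the cut-points and any knowledge or attitude score are not given.

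**The concern.** A level of knowledge has a direction: more is better. Multinomial logistic regression treats categories as unordered labels. With K levels it estimates K-1 arm odds ratios and tests them jointly on K-1 degrees of freedom, so there is no single arm effect, and power is spent on patterns nobody expects. If the levels are only two, that problem disappears, but cutting a graded questionnaire result into two discards information.

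The stake is the first link of the causal chain. The primary hypothesis, in the Background, is that counselling raises knowledge and self-efficacy, which then raise exclusive breastfeeding. The knowledge comparison is the trial's evidence on that first step. An inefficient analysis makes it more likely that a true shift is reported as not shown.

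**Working it through.** **1. The plan's own sample size.** Inputs (Sample size considerations): 2% against 12%, two-sided 5%, power 80%, design effect 3.2 from ICC 0.05, attrition 20%.

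- Per arm: (1.960 + 0.842)² × (0.02×0.98 + 0.12×0.88) / 0.10² = 98.3, so about 196 in total, as stated.
- With clustering: 196 × 3.2 = 627. With attrition: 627 / 0.8 = 784, against the stated figure of about 780.
- Design effect: 627 / 14 clusters is about 45 women each, and 1 + (45 - 1) × 0.05 = 3.2, as stated.

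This calculation concerns exclusive breastfeeding only. The article states no power, effect size or ICC for knowledge and attitudes.

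**2. Effective size for the knowledge comparison.** 780 × 0.8 / 3.2 = 195, or about 98 women per arm. This borrows the breastfeeding ICC, which is an assumption.

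**3. Reference effect.** Assume a normal underlying score with a shift d between arms. A score comparison has non-centrality n·d²/2. With n = 98 and d = 0.40 this is 98 × 0.16 / 2 = 7.84, which gives 80% power. The value 0.40 SD was chosen to set that benchmark and does not come from the article.

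**4. The same shift cut into K equal-sized levels.** With level probabilities p0 and p1 in the two arms and mean p̄, the multinomial likelihood-ratio test has non-centrality 2n[Σ p0 ln(p0/p̄) + Σ p1 ln(p1/p̄)] on K-1 degrees of freedom. For K = 3, p0 = (0.409, 0.327, 0.264) and p1 is the reverse. The ordered comparison is a one-degree-of-freedom trend test on rank scores, standing in for a proportional-odds model.

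| Levels | Multinomial non-centrality (df) | Multinomial power | Ordered non-centrality (1 df) | Ordered power |
|---|---|---|---|---|
| 2 | 4.95 (1) | 60% | 4.93 | 60% |
| 3 | 6.14 (2) | 60% | 6.10 | 70% |
| 4 | 6.65 (3) | 57% | 6.56 | 73% |
| 5 | 6.93 (4) | 54% | 6.80 | 74% |

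With skewed levels, multinomial power is 54%, 53% and 51% for three, four and five levels, ordered power is 64 to 71%, and two-level power is 56%.

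**5. Where the loss comes from.** With equal levels, ignoring order costs 10 points at K = 3, 16 at K = 4 and about 20 at K = 5. Categorising costs a further 10, 7 and 6 points, which an ordinal model would also lose. At K = 2 all of the loss (about 20 points) comes from dichotomising.

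**6. Sensitivity** (score against multinomial, three to five equal levels):

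| ICC | Effective n per arm | Shift (SD) | Score | Multinomial |
|---|---|---|---|---|
| 0.10 | 58 | 0.40 | 58% | 33 to 38% |
| 0.05 | 98 | 0.30 | 56% | 32 to 37% |
| 0.05 | 98 | 0.50 | 94% | 75 to 80% |
| 0.05 | 98 | 0.70 | nearly 100% | 97 to 98% |
| 0.01 | 219 | 0.40 | 99% | 90 to 92% |
| 0 | 315 | 0.40 | 99.9% | 98% |

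All figures are large-sample approximations for one measurement per woman. They omit baseline adjustment, repeated measures and a correction for having only 14 clusters.

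**The case against.** The strongest reply is that the entry in Table 2 sits beside three outcomes and may be meant for the practice rates and durations in the second and third. On that reading knowledge has simply not been given a model, and a condensed article may leave that to a fuller plan. The reply has some force, but it does not clear the table. The table presents itself as the detailed outline, lists knowledge levels first, and offers nothing else for that objective. The text's own list of secondary outcomes for comparison does not mention knowledge or attitudes either.

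Second, the article uses the multinomial label for a yes/no primary outcome, and Table 2 uses it for stunting, underweight and wasting, each defined by one cut-off. It may therefore mean ordinary logistic regression. This stands. A reader might infer that several, possibly conflicting, odds ratios are certain. They are not, because the number of levels is unstated. The two-level reading removes the ordering loss but not the loss against a score.

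Third, a reader might infer that the text already names a score analysis for knowledge and that Table 2 departs from it. The documents do not support this: the only examples given for ANCOVA are breastfeeding durations, and no knowledge or attitude score is mentioned. If a score were built, the general rule for continuous variables would cover it, but Table 2 refers to levels.

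Fourth, the power figures are constructed. That is fair, and they are shown as conditional for that reason.

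**Conclusion.** The point holds as a mismatch between outcome and method in one table row. Whether the label is read literally or as two-level logistic regression, the listed method uses less of the information than a score would. With three or more levels it also uses less than an ordinal model would.

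At ICC 0.05, 98 effective women per arm and a 0.40 SD shift, the shortfall against a score is roughly 20 to 26 points of power with equal levels. An ordinal model would recover 10 to 20 of these when there are three to five levels. It would be wrong to say that power certainly falls well below that of a score: the gap is about 2 points at ICC 0, 7 to 9 at ICC 0.01, and 2 to 3 with a 0.70 SD shift. The number of levels, the effect and the ICC for knowledge are all assumptions.

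The consequence is confined to a secondary outcome. The primary outcome and the target of 780 are untouched. This is a cheap improvement and not a threat to the trial's main conclusion.

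**What to change.** In Table 2, objective 1, outcome 1, state the scale and a matching model:

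- Where the questionnaire items support a score, compare knowledge and attitude scores between arms by ANCOVA or a linear mixed model, adjusted for the value collected at recruitment and with a community-unit random effect. Report one mean difference with its 95% confidence interval.
- If ordered levels are kept, state their number and cut-points. Use ordinal (proportional-odds) logistic regression that allows for clusters, with one common odds ratio.
- Keep logistic regression for the feeding indicators that really are binary.

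The cost is one row of wording and no new data collection. The instrument is not shown, so whether the items add up to a usable score has to be confirmed. The small downside is that a mean score difference is less familiar to policy readers than a percentage with good knowledge, which can still be shown descriptively.

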The elements of counselling package are based on WHO/UNICEF IYCF guidance documents, training and other materials, including the Infant and Young child feeding counselling integrated course [32]. The package is designed to equip community workers or primary health care staff to be able to support mothers, fathers and other caregivers to optimally feed their infants and young children. The CHWs will be equipped with infant and young child feeding counselling cards; brightly coloured illustrations that depict key infant and young child feeding concepts and behaviours for the CHWs to share with mothers, fathers and other caregivers. The package will be adapted to include counselling messages on maternal nutrition.

Counselling will be initiated during pregnancy as soon as the mother is recruited and will be continued until the end of infancy (one year after delivery). Counselling will encompass maternal nutrition, immediate initiation of breastfeeding after birth, breast positioning and attachment, exclusive breastfeeding, frequency and duration of breastfeeding, expressing breast milk, storage and handling of expressing and lactation management. It will also focus on age-appropriate complementary feeding, starting at six months: age appropriate complementary foods (nutritious, safe, affordable, and locally available), feeding frequency and quantity, and appropriate feeding practices including hygiene and responsive feeding behaviours, which encourage mother-child interaction during feeding [33,34]. For the intervention arm, CHWs will visit the pregnant woman about once every month up to week 34, after which they will visit the mother weekly until delivery. After delivery, they will visit the mother weekly in the first one month, then once a month until the end of infancy, but during the fifth month when mothers are expected to initiate complementary feeding, the frequency will be biweekly.

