### Other data to be collected

Other data to be collected will include:

1. Baseline data; collected at recruitment before the commencement of the intervention in both the control and intervention arms. Baseline data will include:

1.a. Knowledge, attitudes and practices regarding maternal and infant feeding.

1.b. Maternal anthropometric measurements.

1.c. Household food security.

1.d. Maternal socio-demographic characteristics and socio-economic status.

2. Child motor development (self-reported by the mother using questionnaire); updated every two months during the follow-up period after delivery.

3. Dietary intake for the mother collected every two months during the follow-up period through an interviewer administered questionnaire to the mother.

4. Maternal weight, monitored every two months during pregnancy and in the first year after delivery.

5. Contextual data, including morbidity from common childhood illnesses, antenatal care, place of delivery, vaccination, household food security, water and sanitation and hygiene practices will be collected through an interviewer administered questionnaire to the mother; updated every two months (where relevant) during the follow-up period.

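### Table 2's control list for the infant growth outcomes leaves out maternal size at recruitment, a pre-intervention measure the trial already collects; prespecifying it is a cheap but modest improvement.

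*Protocol article*

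**What the plan says.** Table 2 of the protocol article (Statistical analysis) gives the same control variables for objective 2 (stunting, underweight, wasting) and objective 3 (diarrhoea): "SES, food security, maternal demographic characteristics, child morbidity, antenatal care, vaccination status". Objective 2 is to be analysed by multinomial logistic regression and objective 3 by multilevel modelling.

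Under Other data to be collected, baseline item 1.b is "Maternal anthropometric measurements". The baseline data are "collected at recruitment before the commencement of the intervention in both the control and intervention arms". Item 1.d lists maternal socio-demographic characteristics separately, so the demographic entry in Table 2 does not naturally cover body size. Item 4 is repeated maternal weight through pregnancy and the first year.

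Water and sanitation sit elsewhere, in item 5 (contextual data, updated every two months where relevant): "household food security, water and sanitation and hygiene practices will be collected through an interviewer administered questionnaire to the mother".

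The Statistical analysis text describes adjustment for baseline measures and "prognostic factors (for example, Socio-economic status (SES) and household food security", to be made "if randomization of the clusters does not control for differences in these factors at baseline".

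**The concern.** A mother's size before counselling cannot be changed by the intervention and is a plausible predictor of her infant's length and weight. Adjusting for it introduces no bias. It can recover some power and it guards against a chance difference between arms. With seven community units per arm, and stratification only on slum and cluster size, such a difference is quite possible.

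Table 2 goes as far as naming covariates for each objective, yet it omits this one. The text then leaves adjustment to depend on whether an imbalance is seen, so the decision would be taken after looking at the data. At stake are the power and credibility of the growth comparisons, which are secondary outcomes.

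**Working it through.** **1. The plan's own figures (Sample size considerations).** Inputs: exclusive breastfeeding rising from 2% "to 12%; a ten percentage point increase"; two-sided 5% level; 80% power; ICC 0.05; design effect 3.2; 20% attrition; 14 clusters.

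- Per arm: (1.960 + 0.842)² × (0.02×0.98 + 0.12×0.88) / 0.10² = 98.3, so 196.5 in total (stated: 196).
- 196 × 3.2 = 627.2 analysed pairs; 627.2 / 14 = 44.8 per cluster; 1 + 43.8 × 0.05 = 3.19 (stated: 3.2).
- 627.2 / 0.8 = 784 (stated: about 780).

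The figures reproduce. They concern exclusive breastfeeding, so growth covariates do not touch them. The article gives no ICC, power or explained variance for growth or diarrhoea; everything below rests on assumed values.

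**2. Standard error on a linear scale.** Borrow ICC = 0.05 (stated for breastfeeding, assumed here for growth) and m = 44.8. With total variance set to 1, the variance of a cluster mean is

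V = ICC × (1 − R²b) + (1 − ICC) × (1 − R²w) / m,

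where R²w and R²b are the additional within- and between-cluster variance explained, beyond the covariates already listed.

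Without maternal size: V = 0.05 + 0.95/44.8 = 0.0500 + 0.0212 = 0.0712. The between-cluster share is 0.0500/0.0712 = 70%.

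| R²w | R²b | V | Fall in SE |
|---|---|---|---|
| 4% | 0 | 0.0704 | 0.6% |
| 12% | 0 | 0.0687 | 1.8% |
| 4% to 12% | 20% | 0.0604 to 0.0587 | 8% to 9% |
| 4% to 12% | 50% | 0.0454 to 0.0437 | 20% to 22% |

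Letting R²w run from 0 to 20% widens the last two rows to 7%–11% and 19%–23%. The 4% to 12% range corresponds to an assumed correlation of 0.20 to 0.35 between maternal size and infant z-score (0.20² = 4%; 0.35² = 12.25%).

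**3. Logistic models.** The linear argument does not carry over directly to objective 2. A simulation used 624 infants (780 × 0.8), no clustering, an intervention log odds ratio of −0.45 and 600 replicates per row:

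| Covariate effect (log odds per SD) | SE of log odds ratio, without → with covariate | Mean estimate | Power |
|---|---|---|---|
| 0.3 | 0.169 → 0.171 | −0.438 → −0.449 | 75.0% → 75.3% |
| 0.6 | 0.168 → 0.175 | −0.413 → −0.450 | 69.0% → 73.8% |
| 1.0 | 0.167 → 0.184 | −0.380 → −0.462 | 63.8% → 71.0% |

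The standard error rises slightly. Power improves because the conditional odds ratio lies further from 1. The power levels themselves do not apply to this trial, since clustering is left out; only the direction is informative.

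**4. Chance imbalance.** If maternal size also had an ICC of 0.05 (assumed), and ignoring stratification, the difference in arm means would have a standard error of √[(2/7) × 0.0712] = 0.14 SD. With 624 individually randomised pairs it would be √(4/624) = 0.08 SD. At a correlation of 0.20 to 0.35, a one-standard-error imbalance would move an unadjusted difference in z-score by 0.14 × 0.20 = 0.03 to 0.14 × 0.35 = 0.05 SD.

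**The case against.** The best defence is that nothing here is stated wrongly. Table 2 is presented as an outline, the covariates in the text are given as examples of open classes, and a full analysis plan may settle the list. That stands in part: the article does not exclude maternal size, so this is an improvement and not a contradiction. It is not a full answer, because Table 2 does name covariates by objective and the text does tie adjustment to observed imbalance.

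Three stronger readings are tempting, and the document does not support them.

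- A reader might infer that the strongest predictors of growth and diarrhoea have been left out. The article nowhere ranks predictors or gives a correlation.
- A reader might turn the assumed correlations into 4% to 14% more pairs (1/(1 − r²) − 1, or 26 to 87 on 624) and conclude that much precision is lost. Those would be extra pairs inside the same 14 clusters, where about 70% of the variance of a cluster mean is untouched. The calculation also assumes a linear model, whereas logistic regression is planned, and it ignores overlap with SES, food security and maternal demographics already listed.
- A reader might extend the point equally to water and sanitation for diarrhoea. These are contextual items and not in the baseline list, so a recruitment value is not established. Hygiene is itself counselled ("appropriate feeding practices including hygiene and responsive feeding behaviours"), so values recorded during follow-up may reflect the intervention.

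**Conclusion.** The point holds for maternal size in the growth models, at low severity. Table 2 omits a measure that is recorded before the intervention in both arms, and adjustment as written waits on observed imbalance.

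The size of the gain cannot be derived from the document. Under the assumed ICC and cluster size it is small if maternal size acts only within clusters. It becomes material only if maternal size also accounts for a sizeable part of the differences between community units, for which the article offers no evidence. In the logistic models the return is some power and protection against chance imbalance.

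The omission does not bias the planned comparisons and does not invalidate the analysis. The primary outcome and the sample size are unaffected. For diarrhoea the point is conditional on a recruitment value existing.

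**What to change.** In Table 2, objective 2, name one maternal size measure taken at recruitment as a fixed covariate in every growth model, whether or not the arms differ on it. Choose it from the measures actually collected, since the article does not list them, and prefer one little affected by gestation because the women are measured while pregnant. Do not use maternal weight recorded after recruitment: the counselling covers maternal nutrition and could change it.

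In objective 3, add water source and toilet type only if a value was recorded at recruitment. Do not adjust for hygiene practices recorded during follow-up.

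The cost is a change of wording in Table 2 or the analysis plan, one or two extra parameters and a few missing baseline values to handle. The maternal measure needs no new data collection. The article reports that recruitment is still under way, so the change can be fixed before analysis.
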